## Abstract

Multi-modal neuroimaging techniques have the potential to dramatically improve the diagnosis of the level consciousness and prognostication of neurological outcome for patients with severe brain injury in the intensive care unit (ICU). This protocol describes a study that will utilize functional Magnetic Resonance Imaging (fMRI), electroencephalography (EEG), and functional Near Infrared Spectroscopy (fNIRS) to measure and map the brain activity of acute critically ill patients. Our goal is to investigate whether these modalities can provide objective and quantifiable indicators of good neurological outcome and reliably detect conscious awareness. To this end, we will conduct a prospective longitudinal cohort study to validate the prognostic and diagnostic utility of neuroimaging techniques in the ICU. We will recruit 350 individuals from two ICUs over the course of 7 years. Participants will undergo fMRI, EEG, and fNIRS testing several times over the first 10 days of care to assess for residual cognitive function and evidence of covert awareness. Patients who regain behavioral awareness will be asked to complete web-based neurocognitive tests for 1 year, as well as return for follow up neuroimaging to determine which acute imaging features are most predictive of cognitive and functional recovery. Ultimately, multi-modal neuroimaging techniques may improve the clinical assessments of patients' level of consciousness, aid in the prediction of outcome, and facilitate efforts to find interventional methods that improve recovery and quality of life.

## Introduction

Severe acute brain injury is a medical emergency that requires immediate admission to an intensive care unit (ICU) for life-sustaining therapies. Little is known about residual cognitive function in the first few days following injury, which makes both the accurate diagnosis of the level of consciousness and the prognostication of neurological outcome very challenging. Current prognostic tools focus on predicting a poor neurological outcome (a clinical outcome no better than vegetative state or severe disability with total dependency) (1). As it stands, there are no accepted clinical measures used in standard practice that can determine the likelihood of good functional recovery (recovery that allows for sufficient function for independent activities of daily life) (2). However, recent research has suggested that advanced neuroimaging methods, such as structural imaging (diffusion-weighted and diffusion-tensor) may provide additional prognostic information that is not currently attainable using standard clinical measures (3–5). There is also a lack of reliable diagnostic tools for assessing the level of consciousness a patient retains while in the ICU. Subjective bedside behavioral assessments are primarily used, which can be confounded by sedative and analgesic medication that are given to patients to tolerate mechanical ventilation, facial and ocular injuries, and their inter-rater reliability has been called into question (6, 7). Accurately classifying the level of consciousness at the bedside is imperative, as a growing body of research suggests that these patients may have a period of dissociation between regaining awareness and behavioral responsiveness (8, 9). To this end, there is a need to develop methods that can be deployed in the ICU to accurately assess residual cognitive function in the early days of injury, thereby improving patient care and inform clinical decision making.

Multi-modal imaging techniques may offer new ways for advancing the prognostication and diagnosis of critically ill patients in the ICU. Functional magnetic resonance imaging (fMRI) has been used to assess the integrity of passive perceptual and higher-order cognitive abilities in chronic disorders of consciousness, such as patients in a vegetative state and unresponsive wakefulness syndrome, who regain wakefulness in the months to years following acute injury but lack overt behavioral function (10, 11). Further, fMRI studies have shown that 15–20% of chronic disorders of consciousness patients can willfully modulate their brain activity in response to command following tasks; suggesting a level of covert awareness that may not be apparent clinically (12, 13). Importantly, fMRI findings have demonstrated prognostic value, as activity in higher-order integrative cortical areas to external stimuli has been associated with improvements in functional recovery (14). While a substantial amount of fMRI research has examined brain activity in chronic patients with disorders of consciousness, few studies have explored its use in an acute intensive care setting (9, 15–18). As such, the full prognostic and diagnostic efficacy of fMRI in this patient population has yet to be determined.

Portable and low-risk modalities, such as electroencephalography (EEG) and functional near infrared spectroscopy (fNIRS), are promising neuroimaging techniques that can be used to assess cortical function at a patient's bedside. High-density EEG is low-cost and readily available in most clinical settings. In this way, EEG is ideal for routine and repetitive assessments of neural function in patients with severe brain injury. Moreover, EEG has been used extensively in patients with chronic disorders of consciousness to assess residual cognitive function (19, 20). In an acute setting, neural responses have shown some promise in predicting outcomes by assessing basic auditory function and covert speech comprehension (21, 22). FNIRS is also an attractive option for assessing brain activity in the ICU and is often considered the optical equivalent of fMRI. This method is a non-invasive optical technique that maps local changes in neural blood oxygenation in response to stimuli and at rest. Near infrared spectroscopy is a feasible tool for detecting neural activity following acute brain injury (23) and has been used as a communication modality with non-responsive patients in the ICU (24).

Utilizing a variety of imaging techniques (fMRI, EEG, fNIRS) together to assess neurophysiologic function offers new opportunities to study the brain following severe injury. Indeed, multiple neuroimaging modalities and tasks increase the chances of detecting residual cognitive function in patients with chronic disorders of consciousness (25). In an acute setting, one specific method may not be suitable for all patients, as the injuries of some individuals will render them ineligible for testing with certain neuroimaging modalities. For example, patients with metallic implants and raised intracranial pressure will be incompatible with fMRI, craniotomies and drains can impede EEG and fNIRS placement leading to abnormal recordings, and large bleeds can prevent the fNIRS probes from detecting a reliable signal.

This research protocol outlines a novel multimodal imaging program using all three imaging methods (fMRI, EEG, fNIRS) that aims to improve the diagnosis and prognosis of acutely unresponsive, brain injured patients. Critically ill patients will undergo testing several times over the course of the first 10 days of ICU stay to meet the following objectives:

To establish whether fMRI can aid prognostication in acute disorders of consciousness.To establish whether fMRI measures of covert awareness can be used in the diagnosis of acute disorders of consciousness in the ICU.To develop bedside methods (EEG, fNIRS) for assessing residual cognitive function and covert awareness in the ICU and establish whether these measures can supplement diagnosis and prognostication.To Explore the use of bedside technology for communicating with select patients with acute brain injury.

The overarching hypothesis is that a subset of critically ill patients will show detectable neural responses to external stimuli and that this activity will be related to improved clinical outcomes and the recovery from acute brain injury. We also predict that a proportion of patients will be able to willfully modulate their brain activity in response to command following tasks, suggesting a level of covert awareness that may not be detectable with clinical examination alone. We anticipate that this multimodal research program will provide critical insight into neural function following severe brain injury and ultimately allow clinicians to render a more accurate diagnosis and prognosis for patients in the ICU.

## Materials and Methods

### Ethics

Ethical approval for this research study was obtained by the Health Sciences Research Ethics Board of Western University (project identification number: 114967). All study procedures will be performed per relevant guidelines and regulations and in accordance to the 1964 Declaration of Helsinki. Written informed consent will be obtained by the next of kin, as the patient population of this study will be unable to consent for acute imaging procedures. Patients will be asked to reconsent to the study if they regain the capacity to provide consent before longitudinal cognitive testing and imaging.

#### Healthy Controls

Up to 50 age and sex matched healthy controls will be recruited in this study. Data acquired from these participants will used as a reference of typical neural activity for the neuroimaging paradigms in this study.

#### Feasibility

The sample size for this study was determined based on feasibility. We accounted for the estimated ICU survival rates for various common severe brain injuries, loss of data due to poor quality (~5–10%), and the potential of withdrawal from study procedures before, during, or after testing commences for various reasons (patient regains awareness before imaging procedures are complete, decline of reconsent, unexpected medical complications). Based on admission information obtained from support services at London Health Sciences Centre, we can expect approximately 550–650 patients admitted into the ICU with a life threating brain injury that requires mechanical ventilation each year. To this end, over 7 years we can expect approximately 4,200 patients that may be eligible for this study. As such, we are confident that 350 patients is an appropriate and feasible number for this study. Furthermore, this project will have a fulltime research coordinator who will work closely with the bedside nurses and attending physicians to schedule and ensure testing takes place at the correct and appropriate time. The research coordinator will also schedule and administer follow-up cognitive testing and telephone questionnaires.

### Protocol

#### Acute Imaging

Study procedures will commence on days 2–3 after ICU admission with both EEG and fNIRS testing for a total test duration of 2 h within the 48-h period. These 2 h of testing will occur at some point on either day 2 or 3 of ICU admission. Between days 4–6, eligible participants will undergo fMRI, EEG, and fNIRS testing. Where possible, fMRI will occur immediately following clinically required structural imaging. The total test duration will be 3 h in the 72-h period, meaning that 3 h of testing will occur across day 5–7 of ICU stay. EEG and fNIRS testing will be repeated between days 7–10 with a testing duration of 2 h. The order of fNIRS and EEG testing will be randomized and counterbalanced for each time point. Stimuli will also be presented in a randomized fashion. Where clinically feasible, all stimuli will be presented with each imaging modality for each timepoint. The overall protocol timeline is detailed in Figure 1.

**Figure 1 F1:**
[figure not shown]
Timeline of overall protocol. After 2–3 days in the ICU, patients will undergo both EEG and fNIRS testing. Between days 4–6 participants will undergo EEG, fNIRS, and fMRI testing. EEG and fNIRS testing will be repeated between days 7 and 10. The order of stimuli presented will be randomized and counterbalanced across all imaging modalities and time points. The order in which imaging modalities will be used at each time point across the timeline will also be counterbalanced and randomized. Patients will undergo neurocognitive testing using the Cambridge Brain Sciences (CBS) cognitive battery once in hospital when delirium has resolved, and then monthly for up to 12 months post injury. Phone assessments to assess functional outcome will take place 3-, 6-, and 12-months post injury.

#### Neurological Examination and Clinical Rating Scales

We will record the following patient demographics: age, sex, occupation, level of education, ethnicity, languages spoken, handedness, and pre-morbid medical history. We will document the mechanism of injury, severity illness score [SOFA and MODS (26, 27)] injury severity scale (for trauma patients), CT scan and/or MRI findings, clinical EEG/evoked potential findings, the magnitude of intracranial pressure (if monitored, and presence and duration of increased intracranial pressure), sedation/analgesia drug dose equivalents, delirium duration, ICU length of stay, and hospital length of stay. At each imaging time point, we will capture bedside clinical examinations of consciousness using the Glasgow Coma Scale (28), Full Outline of UnResponsiveness Score (FOUR Score) (29), and where feasible, the Coma Recovery Scale-Revised (CRS-R) (30). This will be done immediately before or after imaging occurs.

#### Tracking Neurocognitive and Functional Outcomes

Long-term assessment of neurocognitive function will be obtained through tests of executive function and memory, delivered online via the Cambridge Brain Sciences (CBS) platform (www.cambridgebrainsciences.com) (31, 32). Importantly, the CBS tests have a normative database of over 75,000 participants, as these tests have been taken over 10 million times. The CBS tests will be administered on a laptop or a tablet and are designed to assess deductive and verbal reasoning, episodic memory, visuospatial and working memory, and short-term memory and described in thorough detail elsewhere (33). In brief, these tests are: (1) Spatial Span (short-term memory); (2) Monkey Ladder (visuospatial working memory); (3) Paired Associates; (4) Token Search (working memory and strategy); (5) Odd One Out (deductive reasoning); (6) Rotations (mental rotation); (7) Feature Match (feature-based attention and concentration); (8) Spatial Planning (planning and executive function); (9) Interlocking Polygons (visuospatial processing); (10) Grammatical Reasoning (verbal reasoning); (11) Double Trouble (a modified Stroop task); and (12) Digit Span (verbal working memory) (33).

When patients regain behavioral awareness and are no longer sedated, they will be screened by the bedside nurse daily for delirium, as is the standard of care in our hospital. Participants will be asked to participate in the CBS neurocognitive assessment when they score >4 on the Intensive Care Delirium Screening Checklist (34) indicating that they are not currently experiencing delirium.

Testing will take approximately 20 min to complete. The test series will be given once in the hospital when patients are free of delirium. Following discharge, patients will receive a URL link via email to complete the same test series online monthly for up to 12 months following injury. Standard clinical outcome measures will also be used to track functional outcomes at 3-, 6-, and 12-months post injury through phone interviews using the extended Glasgow Outcome Scale (GOS-E) (35).

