### Statistical Analysis

To establish whether fMRI can aid prognostication in acute disorders of consciousness, imaging results will be related to long term behavioral and cognitive follow up assessments. For the somatosensory and auditory processing task, the Spearman's rank-order correlation coefficient will be used to measure the rank correlation between the extent of acute sensory processing and a patient's behavioral scores at 3-, 6-, and 12-months post- injury, as indexed by the GOS-E. This same method will be used to evaluate the relationship between the degree of acute functional connectivity, as measured by the correlation value to healthy controls, to long term outcome. For the movie narrative, the correlation between individual patients and the healthy control group during the intact clip will be related to long term outcome. The primary outcome will be 12 months post injury, and the secondary outcomes will be at 3 and 6 months. Linear regressions will be performed to investigate the effect of clinical and demographic variables on acute imaging features and patient outcomes. All statistical tests will be corrected for multiple comparisons using a False Discovery Rate. We will also determine the sensitivity, specificity, positive predictive value, and negative predictive value for the imaging procedures outlined in the protocol.

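### The delirium threshold for in-hospital cognitive testing runs against the protocol's own delirium-free condition: a score above 4 on a delirium checklist is read as no delirium

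*Protocol article*

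**What the plan says.** The section Tracking Neurocognitive and Functional Outcomes describes how patients reach cognitive testing. Once they are behaviorally aware and off sedation, "they will be screened by the bedside nurse daily for delirium, as is the standard of care in our hospital". They are then invited to the CBS battery "when they score >4 on the Intensive Care Delirium Screening Checklist (34) indicating that they are not currently experiencing delirium".

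The next paragraph of that section gives the timing in words: "The test series will be given once in the hospital when patients are free of delirium". The Figure 1 legend agrees, placing the battery "cognitive battery once in hospital when delirium has resolved, and then monthly for up to 12 months post injury".

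The Statistical Analysis section then says that, for the fMRI prognostic objective, "imaging results will be related to long term behavioral and cognitive follow up assessments".

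**The concern.** The threshold and its stated meaning do not fit each other. The instrument is named as a screening checklist for delirium and is used that way every day, so points would be expected to accumulate as signs of delirium are found. A score above a threshold should then indicate delirium, but the sentence reads it as absence of delirium.

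This is the only numerical rule in the article for deciding when a patient is ready for the CBS battery, and a coordinator or a case report form would work from the number. What is at stake is the validity of the in-hospital cognitive session. Taken during delirium, it reflects the delirium as well as the cognitive effect of the injury. If patients who are clear are not tested, its missingness is tied to the clinical state that it should be free of.

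**Working it through.** No sample-size or power figure is involved ("The sample size for this study was determined based on feasibility"), so the check is one of direction.

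**Inputs from the article**

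| Source | Condition for in-hospital CBS testing |
|---|---|
| Tracking Neurocognitive and Functional Outcomes, numerical rule | Checklist score above 4 |
| Same sentence, stated meaning | No current delirium |
| Same section, following paragraph | No delirium at testing |
| Figure 1 legend | Delirium resolved |

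Three statements of intent agree. Only the inequality differs, and no other part of the article gives a cut-off or defines the scale.

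**Assumption.** The article does not print the scoring key. I take the score *s* to rise with the number of delirium signs and a positive screen to be *s* ≥ *c* for some cut-off *c*. The direction is inferred from the instrument's name and its use as a delirium screen. The value of *c* is left open.

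**Step 1: what the intent requires.** Test when *s* < *c*, which selects the low end of the scale.

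**Step 2: what the rule selects.** Test when *s* > 4, meaning 5 and above. It excludes 0 to 4.

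**Step 3: compare across possible cut-offs.**
- If *c* is 5 or lower, every admitted score (5 and above) is a positive screen, and every negative screen (below *c*, hence 4 or less) is excluded. The rule then admits no clear patient at all.
- If *c* is above 5, the rule admits all positive screens plus the negatives from 5 up to *c* − 1. It still excludes the clearest patients, those scoring 0 to 4.
- No value of *c* makes *s* > 4 select the same patients as *s* < *c*, because one keeps the top of the scale and the other the bottom.

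**Illustration, on an assumed scale.** With a range of 0 to 8 and *c* = 4, the rule admits 5, 6, 7 and 8 (all positive) and excludes 0, 1, 2 and 3 (all negative). A score of exactly 4 is positive and also excluded. The range and cut-off are assumptions, and the conclusion on direction does not depend on them.

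**Step 4: the only reading that rescues the sentence.** It would be coherent if a higher score meant less delirium. Nothing in the article supports that, and it does not suit a checklist used to screen for delirium.

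**Step 5: what depends on the rule.** The Spearman correlations named in the Statistical Analysis section use the GOS-E at 3, 6 and 12 months, with 12 months primary. The good-outcome cut-off is also on the GOS-E, and the linear classifier separates survivors from non-survivors. None of these uses the delirium threshold. What remains exposed is any analysis that relates imaging to the in-hospital CBS session.

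**The case against.** The strongest reply is that this is a symbol error whose meaning is plain. The sentence states its own intent, two other statements agree with it, and the bedside nurses already use delirium screening as routine care. They are unlikely to call a positive screen negative because of one character in an article. The full protocol and case report form are not shown and may carry the correct rule. This stands as a limit on the harm, which arises only if the number is followed against the words. It does not make the printed threshold right.

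A reader might infer several stronger things that the article does not support:

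- **That every in-hospital CBS session is compromised.** Nothing shows that any session was run under the literal rule.
- **That a cognitive baseline and all changes from it are biased.** The article never calls the in-hospital session a baseline and specifies no change-from-baseline or recovery-slope analysis. It says only, in general terms, that imaging will be related to cognitive follow-up.
- **That the monthly online tests are also affected, or are certainly safe.** They have no separate checklist rule. The threshold is attached to the invitation to CBS testing, and the article does not say whether that covers only the hospital session.
- **That reconsent would be sought from delirious patients.** The Ethics section ties reconsent to regained capacity, which is a separate condition.
- **That the correct cut-off is known.** The article gives none, so the check supports a change of direction and no particular number.

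**Conclusion.** The point holds as a contradiction between a printed decision threshold and the condition that it is meant to implement. It is not missing detail that a fuller document would supply, because the article gives both the number and its interpretation and they conflict.

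Applied as written, the rule would offer the in-hospital CBS session to patients who screen positive for delirium and withhold it from those who are clear. Screening is daily, so a patient passing from delirium to clarity would qualify on the earlier, delirious days, and a patient who never exceeded 4 would not qualify at all. Any analysis relating imaging to that session would be biased. The direction and amount of bias cannot be derived from the article, which gives neither the number of patients expected to reach this step nor the frequency of delirium.

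The reach is one in-hospital session on a cognitive measure, conditional on literal use of the number. The GOS-E outcomes, including the 12-month primary, are untouched. The conclusion rests on one assumption, that a higher checklist score means more signs of delirium.

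**What to change.** 1. Reverse the direction of the threshold so that it agrees with the delirium-free condition stated elsewhere in the section and in the Figure 1 legend.
2. Take the exact cut-off, and the handling of a score of exactly 4, from reference 34 and the ICU's own screening form, and print them in the protocol.
3. Check whether the case report form carries the same inequality and correct it if so.
4. State whether the rule governs only the in-hospital session or the CBS invitation as a whole.
5. For any in-hospital CBS session already done, look up the recorded checklist score, flag sessions done on a positive screen, and repeat any analysis using them without the flagged sessions as a sensitivity analysis. Outright exclusion is not warranted on present evidence.

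The cost is a short wording correction and a look-up of existing records. No new data collection is needed, because delirium is already screened daily in routine care.
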